**Fig 2 pone.0286885.g002:**
[figure not shown]
Study flow diagram, adapted from CONSORT.

### BASMI

The index that groups four axial measurements (cervical rotation, Schober test, lateral torso flexion, tragus-to-wall distance) also includes a measurement of peripheral mobility (intermalleolar distance) [29]. These variables will be measured comparatively at least twice to obtain the mean measurements to calculate the final score based on a table of 11 points [25]. This index is evaluated by the examiner and conveys spinal and peripheral mobility findings in centimeters and degrees [27, 30].

### BASFI

The BASFI questionnaire is self-administered and consists of 10 questions investigating the functional status of the person diagnosed with AxSpA. Each question can be scored from 0 to 10, with 0 corresponding to no limitation in carrying out the proposed activity and 10 corresponding to the absolute impossibility of carrying it out. This scoring system employs a visual analog scale scored on a horizontal metric line [31]. The final score is obtained from the sum of the results of the questions divided by 10. This instrument is validated for use in Spanish in Colombia [32, 33].

### BASDAI

The BASDAI evaluation is self-administered and consists of six questions inquiring about issues related to the five main symptoms of AxSpA: fatigue, axial pain, joint pain and/or edema, enthesis pain, and morning stiffness [34]. Similar to the BASFI, it is based on a visual analog scale measuring 10 centimeters in a horizontal line. It is scored by adding the scores for questions 1 to 4; for questions 5 and 6, the mean is calculated, and finally, the scores of all questions are added and divided by 5. A higher BASDAI score suggests more active disease [27]. This questionnaire is also validated in Spanish [34].

### AsQoL

The AsQoL is self-administered and validated in Spanish in Colombia. It consists of 18 questions with the possibility of dichotomous answers (YES—NO). The affirmative answers are scored as 1, and the negative answers are scored as 0. The overall score is the sum of the scores for each question and can be between 0 (better health-related quality of life) and 18 (worse health-related quality of life). If more than three questions are unanswered, the overall score cannot be calculated [35].

### Recruitment

The people who will be eligible for the study are those receiving some medical or therapeutic service in the clinic selected for the study. A research assistant will review the medical records of people with an AxSpA diagnosis confirmed by a rheumatologist. Individuals who are potentially eligible will be contacted by telephone, and the intention and scope of the study will be briefly explained. After this communication, if a person verbally expresses their desire to be part of the research process, a face-to-face interview will be scheduled.

### Sample size

The sample size was calculated in the program R Studio version 3.5.3, package of superiority clinical trials, based on a mean difference of 4.0 in the BASMI with a standard deviation of 2, an r (ratio) between groups of 1, and assuming a loss of 20%. An alpha one sided of 0.05% and a power of 0.80 were estimated based on mean difference test corresponding to a clinical trial of superiority (repeated measures ANOVA). The total number of people was 82 (42 per arm). Non probabilistic purposive sampling will be used.

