**Methods:**

In this randomized controlled parallel superiority clinical trial, 84 people with an AxSpA diagnosis confirmed by a rheumatologist will be randomly assigned to groups: the experimental group or the control group. The experimental group will receive myofascial induction, and the control group will undergo a simulation of the technique. Both groups will receive an examination session and six intervention sessions twice per week for three weeks. A baseline follow-up will be performed immediately after the intervention and four weeks after treatment.

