### Statistical analysis

The data will be analyzed in the latest version of the R Studio program. A statistical analysis will be performed based on the purposive analysis principles. The assumption of normality for the quantitative variables will be verified with the Shapiro–Wilk test, followed by a descriptive analysis; for the continuous variables, measures of central tendency or dispersion according to the data will be applied. For categorical variables, the proportions and frequencies will be calculated. Differences between the groups in measurements for the primary and secondary objectives will be analyzed by repeated measures ANOVA the variables with a normal distribution. Nonparametric tests will be performed if the data do not comply with the assumption of normality, interaction of arm by time effect will not be tested. Qualitative variables will be evaluated with the chi-square test of independence or Fisher’s exact test, as appropriate. For all tests, a significance level of p <0.05 will be employed.

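### The sample-size inputs as printed (BASMI difference 4.0, SD 2, power 0.80, 20% loss) do not yield 82 or 84 participants, so the difference the trial has 80% power to detect is unknown

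*Protocol article*

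**What the plan says.** The Sample size section of the protocol article gives a full set of inputs and a result. The calculation is "based on a mean difference of 4.0 in the BASMI with a standard deviation of 2", with "an r (ratio) between groups of 1" and an assumed loss of 20%. On error rates it says: "An alpha one sided of 0.05% and a power of 0.80 were estimated". The test is described as "based on mean difference test corresponding to a clinical trial of superiority (repeated measures ANOVA"), and the software as an R package for superiority trials. No superiority margin, within-person correlation or dropout formula is given.

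The result reads: "The total number of people was 82 (42 per arm"). The Methods part of the Abstract instead says "84 people with an AxSpA diagnosis confirmed by a rheumatologist will be randomly assigned to groups". The Statistical analysis section adds: "For all tests, a significance level of p <0.05 will be employed". It does not say whether that level is one-sided or two-sided.

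**The concern.** A difference of 4.0 with SD 2 is a standardised effect of 2.0, which a very small two-arm trial can detect. Forty-two per arm is far more than such an effect needs at 80% power. The total and the per-arm figure also disagree, and the alpha is printed as a percentage that is one hundredth of the level in the analysis section.

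BASMI is the primary outcome, and this section is the only place where the article says what effect the trial is designed to detect. If inputs and result do not belong together, a reader of the finished trial cannot tell which difference it had 80% power for. Nor can the reader tell whether an observed difference of, say, 1.5 points met the planning target or fell well short of it.

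**Working it through.** **Inputs (Sample size section).** Difference 4.0, SD 2, ratio 1, power 0.80, loss 20%, alpha one-sided and printed as 0.05%. I read alpha in three ways: one-sided 0.05 (the percent sign is a slip), two-sided 0.05 (a common reading of p <0.05 in Statistical analysis), and one-sided 0.0005 (literal).

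**Step 1: try to reproduce the stated size.** Per arm, n = 2(z_α + z_β)² SD²/δ². With SD²/δ² = 4/16 = 0.25, this is n = 0.5(z_α + z_β)², where z_β = 0.842. The t column is the exact noncentral-t answer.

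| Alpha | z_α | n per arm (z) | n per arm (t) | Total after 20% loss |
|---|---|---|---|---|
| One-sided 0.05 | 1.645 | 0.5 × 2.486² = 3.09, so 4 | 4 | 10 |
| Two-sided 0.05 | 1.960 | 0.5 × 2.802² = 3.92, so 4 | 6 | 10 to 16 |
| One-sided 0.0005 | 3.291 | 0.5 × 4.132² = 8.54, so 9 | 12 | 22 to 30 |

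The ranges cover the z and t methods and both ways of allowing for loss. For example, 9 × 1.2 = 10.8 gives 11 per arm (22 in total), and 12/0.8 = 15 per arm gives 30.

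No variant that keeps 4.0 and SD 2 comes close to 82:
- Treating SD 2 as needing a factor √2, at two-sided 0.0005 with the t method, gives 22 per arm. That is 28 after loss and 56 in total, the largest variant found.
- Using repeated measures with assumed correlations from 0 to 0.9 gives at most 9 per arm for the mean of three visits and 19 per arm for a change score, before loss.

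**Step 2: work back from the stated size.** 42 × 0.8 = 33.6, so about 34 evaluable per arm. The standard error of the difference is 2√(2/34) = 0.485, and 4.0/0.485 = 8.25. Even against the literal critical value, 8.25 − 3.29 = 4.96, so power exceeds 0.9999. That holds for every alpha reading at 33 to 42 per arm.

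**Step 3: the difference detectable with 80% power.** At 34 per arm and SD 2, δ = (z_α + z_β) × 0.485:
- One-sided 0.05: 2.486 × 0.485 = 1.21 (t-based 1.22).
- Two-sided 0.05: 2.802 × 0.485 = 1.36 (t-based 1.38).
- One-sided 0.0005: 4.132 × 0.485 = 2.00 (t-based 2.09).

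On the t-based figures, 4.0 is 4.0/2.09 = 1.9 to 4.0/1.22 = 3.3 times the difference that the size supports.

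**Step 4: can the source of 82 and 42 be identified?** At least two different sets of inputs land on 82:
- Effective difference 2, SD 2, one-sided 0.0005: n = 2 × 17.07 = 34.15 per arm, and 2 × 34.15 × 1.2 = 81.96. Rounding up first gives 35, and 35 × 1.2 = 42 per arm.
- Difference 1.2, SD 2, one-sided 0.05: n = 34.35 per arm, and 2 × 34.35 × 1.2 = 82.4.

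The first would arise if a margin of 2 had been subtracted from 4.0. The same standardised effect of 1.0 would arise from 4.0 with SD 4. The article states neither, so these are possible origins only.

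**Step 5: the totals.** 2 × 42 = 84, which agrees with the Abstract and not with 82.

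**The case against.** The strongest reply is that the calculation may have been sound and only its report incomplete. The section names software for superiority trials, and superiority formulas can take a margin. With a margin of 2 and the literal alpha, both 42 and 82 appear and differ only in rounding. On that account one input was left out, and neither the target nor the power is wrong.

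Part of this stands. A reader might infer that 4.0 is the wrong target, but the document does not show that. It shows a set of figures that cannot all hold, without showing which one is at fault. The reply does not rescue the text as printed, though. The margin is not stated, and it works only with an alpha of 0.0005, which conflicts with the p <0.05 used for analysis. Nor is this ordinary condensation in an article, because the section gives inputs and a result that do not agree.

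Three other readings go too far:
- **The trial is too small.** It is much larger than a 4.0-point difference requires.
- **A null result could not be read against 4.0.** With power above 99.99% at SD 2, a null result would be strong evidence against a difference that large.
- **A difference of 4.0 is unattainable on an 11-point table.** The section gives a mean difference, not a fall required of each participant, and the article gives no baseline BASMI distribution from which to judge.

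**Conclusion.** The concern holds as an internal inconsistency. The printed inputs need about 10 participants at one-sided 0.05, or 22 to 30 at the literal one-sided 0.0005, against 82 or 84 stated. The printed power of 0.80 does not hold for 4.0 at SD 2 with 42 per arm; the true figure is above 0.9999. If SD 2 is right, 80% power belongs to a difference of about 1.2, 1.4 or 2.1 points, depending on alpha. The 82 contradicts both 42 per arm and the Abstract, and 0.05% contradicts p <0.05.

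The forward totals rest on a two-sample comparison of means with no margin, and the detectable differences also on SD 2 and about 34 evaluable per arm. Counting 35 evaluable (42/1.2) barely moves them: 1.20 instead of 1.22 at one-sided 0.05. The trial's capacity to detect 4.0 is not in doubt. What is lost is the statement of which difference it was sized for.

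**What to change.** Keep enrolment at 84 (42 per arm) and correct 82 to 84 in the Sample size section. Go back to the original calculation and restate the difference, its SD, any superiority margin, alpha with its sidedness, and the dropout formula, so that the number follows from them. The same alpha and sidedness should appear in Statistical analysis.

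If the original inputs cannot be recovered, replace 4.0 with the difference that about 34 evaluable per arm detects with 80% power at the alpha and sidedness actually used. At SD 2 that is about 1.2 points for one-sided 0.05 or about 1.4 for two-sided 0.05. Say openly that the figure was derived from the enrolment. The choice between one-sided and two-sided testing should be made explicitly and not slip in with the correction.

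The cost is protocol wording and a check of the original calculation. No additional participants are needed.

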### Randomization and concealment

In this study, a simple randomization process will be used by assigning random numbers without repetition in Excel. For randomization concealment, opaque, sealed, consecutively numbered envelopes will be used and kept by a single person. An external person will prepare the envelopes. An envelope will be opened in sequence once the participant has completed the baseline physical examination and the corresponding measurements.

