### Inclusion criteria

People of both sexes over 18 years of age.People with a rheumatology-confirmed diagnosis of AxSpA regardless of the level of disease activity.People with the cognitive ability to follow orders.People who agree to participate in the study.

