### Outcomes

The primary outcome will be joint mobility measured by the Bath Ankylosing Spondylitis Metrology Index (BASMI). The secondary outcomes will be the Bath Ankylosing Spondylitis Functional Index (BASFI), Bath Ankylosing Spondylitis Disease Activity Index (BASDAI), and the Ankylosing Spondylitis Quality of Life Questionnaire (AsQol) [27, 28]. Each of these variables will be measured before the intervention, after the intervention, and four weeks after the intervention. The participants will undergo an initial evaluation before randomization. The results will be collected at each time point according to (Figs 1 and 2).

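### Baseline BASMI is measured before allocation but used neither in the simple randomisation nor in the stated analysis, so a chance baseline difference (95% range about ±0.64 to ±0.86 points) carries into the primary comparison

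*Protocol article*

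**What the plan says.** Under Randomization and concealment, the protocol article states that "a simple randomization process will be used by assigning random numbers without repetition in Excel". It names no block, stratum or minimisation factor. Allocation comes after the baseline work: "An envelope will be opened in sequence once the participant has completed the baseline physical examination and the corresponding measurements". The Outcomes section agrees: "The participants will undergo an initial evaluation before randomization". BASMI is the primary outcome and is measured at that visit.

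The Sample size section assumes "an r (ratio) between groups of 1, and assuming a loss of 20" per cent, and prints "The total number of people was 82 (42 per arm"). The Abstract says that "84 people with an AxSpA diagnosis confirmed by a rheumatologist will be randomly assigned to groups".

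The Statistical analysis section plans repeated measures ANOVA for normally distributed variables and nonparametric tests otherwise. It mentions no adjustment for baseline, and it says that an arm-by-time effect will not be tested. That statement is attached to the sentence on nonparametric tests; I read it as applying to the whole analysis.

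**The concern.** Baseline BASMI is likely to be the strongest single predictor of later BASMI, and each participant's value is known when the envelope is opened. Simple randomisation ignores it. That would matter little if the analysis then took it into account, but the stated analysis does not. No baseline covariate is named, and the interaction that would separate change from starting level is excluded. A chance difference between the arms in starting mobility therefore passes, in large part, into the comparison that is meant to show the treatment effect.

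A lesser matter is arm size. The plan gives 42 per arm, but simple randomisation in the strict sense does not fix the totals. The description leaves open whether each envelope is an independent draw or whether the envelopes come from one shuffled list with a set number per arm.

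**Working it through.** **Inputs.** From the protocol article: 42 per arm, ratio 1, and a sample size "based on a mean difference of 4.0 in the BASMI with a standard deviation of 2". Assumed here: a baseline BASMI SD of 2 (borrowed from the planning SD, which the article does not call a baseline SD), with 1.5 as a lower value; approximate normality; and a baseline-to-follow-up correlation r of 0.6 to 0.9 with equal SD at each visit.

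**1. The plan's own figures.** 2 × 42 = 84, which agrees with the Abstract but not with the printed total of 82. Using n per arm = 2(z_α + z_β)²SD²/δ² with δ = 4, SD = 2 and power 0.80:
- One-sided 0.05: 2 × (1.645 + 0.842)² × 4/16 = 3.09, so 4 per arm, and 4/0.8 = 5 after loss.
- One-sided 0.0005 (the 0.05% as printed): 9 per arm, and 9/0.8 = 11.25, so 12 after loss.

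Neither gives 42. That is a separate and larger problem; below I take 42 per arm as the planned number.

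**2. Chance baseline difference d with 42 per arm.** SE = SD × √(2/42) = SD × 0.218.
- SD 2: SE 0.436; 95% range ±1.96 × 0.436 = ±0.86; P(|d| ≥ 0.5) = 0.25; P(|d| ≥ 1) = 0.02.
- SD 1.5: SE 0.327; 95% range ±0.64; P(|d| ≥ 0.5) = 0.13; P(|d| ≥ 1) = 0.002.

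**3. How much of d reaches the estimate.** If all three visits enter the model and arms are compared on their average, the expected shift is d(1 + 2r)/3. For r = 0.6 this is 2.2/3 = 73% of d; for r = 0.9 it is 2.8/3 = 93%. If only the two post-baseline visits are compared, unadjusted, the shift is r × d, or 60% to 90% of d. With baseline BASMI as a covariate, the linear part of this shift is removed.

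**4. What stratifying would do.** A split at the median of a normal variable leaves a fraction 1 − 2/π = 0.363 of its variance within strata. The SE of d is multiplied by √0.363 = 0.603:
- SD 2: 0.436 × 0.603 = 0.263 (±0.52).
- SD 1.5: 0.327 × 0.603 = 0.197 (±0.39).

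**5. Arm size.** With independent 1:1 draws, the size of one arm is Binomial(84, 0.5):
- P(42/42) = 0.087; P(37/47 or worse) = 0.33; P(34/50 or worse) = 0.10; central 95% range 33 to 51.
- Precision loss is 1 − 4n₁n₂/84². At 37/47: 1 − 6956/7056 = 1.4%. At 34/50: 1 − 6800/7056 = 3.6%.
- For an effect with 80% power at 42/42 (one-sided 0.05), power is 79.3% at 36/48, 78.3% at 33/51, and 79.6% on average over all splits.

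With a shuffled list of 42 + 42, the totals are exact if all 84 envelopes are used, and not guaranteed otherwise. With blocks of 4 and 6 in two strata, an unfinished block leaves a difference of at most 3 in each stratum. The worst case is then a difference of 6, or 39/45.

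**The case against.** Simple randomisation with sealed, numbered, externally prepared envelopes is a valid method. Chance imbalance is not bias, and the standard error of a valid test already allows for it. That stands, and it limits the point to imprecision that could be avoided at little cost.

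A reader might infer more than the article supports in three ways:
- **That the arms will rarely be 42 each, against the plan.** The 8.7% holds only for independent draws. Random numbers that do not repeat may well describe a shuffled list with fixed totals. A ratio of 1 is in any case met in expectation, and 42 already includes the loss allowance. The precision at stake is small on either reading.
- **That the inclusion criteria show a wide spread of mobility.** They admit people "regardless of the level of disease activity", but in this protocol disease activity is measured by BASDAI, a symptom questionnaire, and not by BASMI. The criteria set no mobility limit, but the quoted words do not establish the spread. Hence the assumed SD range.
- **That the analysis will certainly ignore baseline.** A statistical analysis plan may exist and may name covariates. The point rests on what the article fixes: the method it names, and the exclusion of an arm-by-time test. If baseline BASMI is already a planned covariate, most of the concern falls away.

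Blocking also has its own drawback. On a shuffled 42 + 42 list, about 2 × 42/43, or 2, final allocations are fully determined. Blocks of 4 and 6 have expected determined tails of 1.33 and 1.5 per block, or about 24 of 84 allocations, if someone knew the block sizes. The therapists are unblinded and there is one centre, so this is real; hiding and varying the block sizes reduces it.

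**Conclusion.** The point holds as a low-cost improvement, not as an error that invalidates the trial. The article leaves baseline BASMI out of the allocation and out of the stated analysis. With 42 per arm and an assumed baseline SD of 1.5 to 2, the chance difference has a 95% range of about ±0.64 to ±0.86 points and a 13% to 25% probability of reaching 0.5 point. For r between 0.6 and 0.9, roughly 60% to 93% of it would carry into an unadjusted arm comparison, depending on which visits enter. This is lost precision and a less readable result, not bias.

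Arm size alone does not justify a change. What it needs is a clear statement of how the list is built.

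**What to change.** - Replace simple randomisation with permuted blocks of randomly varying size (for example 4 and 6), stratified by baseline BASMI below or above a cut-off fixed in advance. The same external person prepares two numbered envelope series. Keep the block sizes from the clinic team and the therapists.
- In the primary analysis, compare post-baseline BASMI between arms with continuous baseline BASMI and the stratum as covariates. The stratum alone is not enough, since a median split leaves about 36% of the baseline variance within strata.
- If simple randomisation is kept, state whether assignments are independent draws or a shuffled list with fixed totals, and whether that list has 82 or 84 places.

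The cost is a new list and a second envelope series, with no extra participants. BASMI must be scored before the envelope is opened, and some predictability remains at block ends. If enrolment has started, leave the allocation as it is and add the baseline covariate before any unblinded look at the data; that alone recovers most of the gain.

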### Blinding

The people who will perform the baseline and final evaluations will not know the randomization sequences, nor will they be involved in the execution of the treatments in the control group or the experimental group. The participants will visually receive the same procedures since the techniques for the control and experimental groups appear the same; accordingly, they will also be blinded. The PTs who will perform the interventions cannot be blinded due to the need to know the principles of the technique and the form of execution to guarantee correct application of the treatment or simulation. The data analysis will be performed by an external evaluator in the intervention and evaluation process.

### Data management

The data obtained from the participants will be recorded in virtual record format on the REDCap platform [36] by means of a double digitization process to avoid errors in data recording. This platform requires a username and password that will be known only to the research coordinator. In the case of any eventuality, the primary source will be contacted, and the value will be corrected. All documents will be safely stored confidentially. Participants will be identified by a specific number or unique test code. The name and any other identifying details will not be included in any part of the database.

